## **METHODS: DATA COLLECTION, MANAGEMENT, AND ANALYSIS**

### **Data collection methods**

A customized eCRF (electronic Case Report Form) will be created for the study. Study data will be collected and managed using REDCap electronic data capture tools hosted at Fondazione Policlinico Universitario A. Gemelli, IRCCS (<https://redcap-irccs.policlinicogemelli.it/>). REDCap (Research Electronic Data Capture) is a secure, web-based application designed to support data capture for research studies, providing 1) an intuitive interface for validated data entry; 2) audit trails for tracking data manipulation and export procedures; 3) automated export procedures for seamless data downloads to common statistical packages; and 4) procedures for importing data from external sources [Ref1: PA Harris, R Taylor, R Thielke, J Payne, N Gonzalez, JG. Conde, Research electronic data capture (REDCap) – A metadata-driven methodology and workflow process for providing translational research informatics support, J Biomed Inform. 2009 Apr;42(2):377-81. Ref 2: PA Harris, R Taylor, BL Minor, V Elliott, M Fernandez, L O’Neal, L McLeod, G Delacqua, F Delacqua, J Kirby, SN Duda, REDCap Consortium, The REDCap consortium: Building an international community of software partners, J Biomed Inform. 2019 May 9 [doi: 10.1016/j.jbi.2019.103208].

**Data management** Each participating site must maintain appropriate medical and research records for this trial and regulatory/institutional requirements for the protection of confidentiality of study subjects. The Principal Investigator is responsible for assuring that the data collected are complete, accurate, and recorded in a timely manner.

**Statistical methods Primary endpoint:**

Based on the above-mentioned design, the comparison of proportion of progression free patients will be made between A vs B through the Fisher exact test at the completion of phase II and phase III.

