| Trial design  | This is a randomized phase II/III study designed to evaluate the efficacy of convalescent plasma, when used in combination with standard therapy to prevent the progression of pneumonia in elderly COVID-19 patients with comorbidities. The trial will start with a screening Phase II trial designed with two-tailed $\alpha=0.2$ . In case of positive result the trial will proceed in a formally comparative phase III trial ( $\alpha=0.05$ ). Three studies have so far reported the use of CCP in ventilated patients without recording adverse events, but data on patients in earlier phase of disease are lacking. For this reason, the first 57 patients will be observed in order to assess preliminarily the safety of CCP in this population. |
| Study setting | Participating centers are: 

– Fondazione Policlinico Gemelli IRCCS (coordinating center)

– Istituto Nazionale Malattie Infettive Lazzaro Spallanzani IRCCS

– Ospedale SS Annunziata, Chieti

                                                                                                                                                                                                                                                                                                                                                                                                                                                                                                    |

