**Sample size**

**Phase II.** To demonstrate that adding CCP to standard therapy is associated with an increase of proportion of patients without progression from 20% (control, Arm B) to 40% (treatment, Arm A), with a 80% power and a two-tailed alpha error of 0.2, 114 (57 per arm) evaluable patients are needed, with an OR for treatment of 0.375.

**Phase III.** To demonstrate that adding CCP to standard therapy is associated with a reduction of the proportion of patients progressing to severe pneumonia from 40% (control, Arm B) to 20% (treatment, Arm A), with a 80% power and a two-tailed alpha error of 0.05, 182 (91 per arm) evaluable patients are needed, with an OR for treatment of 0.375.

Chow, SC, Shao J and Wang H. 2003. Sample Size Calculations in Clinical Research. Marcel Dekker. New York.

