## **METHODS: ASSIGNMENT OF INTERVENTIONS**

### **Allocation and sequence generation**

Treatment allocation will be randomized between arms A and B with a ratio 1:1 and will be the same in phase II and phase III. Randomization sequences will be generated at Fondazione Policlinico Gemelli IRCCS.R through the RedCap web application, uploading the allocation table through the randomization module (ref: <https://www.project-redcap.org/>).

Randomized stratification will be performed according to age (under/over 80 years), and sex.

**Blinding (masking)** The assignment to intervention will be unmasked to all trial participants (care providers, outcome assessors, and data analysts)

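### Optional improvement: Boschloo's exact test at the same alphas and sample sizes would add about 3 to 4 points of power per phase over the Fisher test, which is itself valid

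*Protocol*

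**What the plan says.** The Statistical methods paragraph on the primary endpoint fixes one test for both phases: the progression-free proportions in arms A and B are compared "through the Fisher exact test at the completion of phase II and phase III".

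The Sample size section sets the levels. For Phase II: "with a 80% power and a two-tailed alpha error of 0.2, 114 (57 per arm) evaluable patients are needed". For Phase III: "with a 80% power and a two-tailed alpha error of 0.05, 182 (91 per arm) evaluable patients are needed". The Phase II rates are given as no progression in 20% of controls and 40% of treated patients. The Phase III rates are given as progression in 40% and 20%.

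The trial design entry makes the Phase II result a gate: "In case of positive result the trial will proceed in a formally comparative phase III trial". Allocation is 1:1 in both phases, stratified by age and sex. The protocol does not report the size that the Fisher test attains and mentions no other exact test for this comparison.

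**The concern.** Fisher's test conditions on the total number of events. With 57 or 91 patients per arm, the conditional distribution is coarse enough for the real false-positive rate to lie well below the nominal level. In absolute terms the gap is widest at the Phase II gate, where alpha was set at 0.2 for a screening trial. A loose screening alpha is normally chosen so that a useful treatment is not discarded too easily, and Fisher leaves part of that allowance unused. The same happens on a smaller scale in Phase III.

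What is at stake is efficiency. Another exact test keeps the same guarantee on the false-positive rate and converts the unused alpha into power at no cost in patients.

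**Working it through.** **Inputs.** From the Sample size section: alpha 0.2 two-sided with n = 57 per arm; alpha 0.05 two-sided with n = 91 per arm; rates 20% versus 40%. The two phases state these rates in opposite directions. For equal arms the two-sided Fisher test is symmetric, so 20% versus 40% and 60% versus 80% give the same power (0.8071 either way at n = 57), and the direction does not affect this check. Each phase is treated as a single fixed-sample test with exactly equal arms.

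**Step 1: reproduce the stated sample sizes.** With a pooled rate of 0.3 and a difference of 0.2,

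n = [z(1−α/2)·√(2·0.3·0.7) + z(0.8)·√(0.2·0.8 + 0.4·0.6)]² / 0.2²

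- α = 0.2 (z = 1.2816): n = 46.4, so 47 per arm.
- α = 0.05 (z = 1.9600): n = 81.2, so 82 per arm.

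The continuity correction n′ = (n/4)·[1 + √(1 + 4/(0.2n))]² gives 55.99, so 56, and 90.95, so 91. The stated 57 and 91 therefore match a calculation that already allows for the conservatism of an exact or corrected test.

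**Step 2: exact power of Fisher.** For each table (x, y), compute the two-sided Fisher P value, reject if P ≤ α, and sum Bin(x; n, 0.2)·Bin(y; n, 0.4) over the rejected tables.

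- 57 per arm, α = 0.2: 80.7% (56 per arm gives 79.98%).
- 91 per arm, α = 0.05: 80.8%.

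The promised 80% is met in both phases.

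**Step 3: attained size of Fisher.** The same sum with one common rate p in both arms, maximised over a fine grid of p.

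| | p = 0.2 | p = 0.3 | p = 0.4 | Maximum |
|---|---|---|---|---|
| Phase II, nominal 0.20 | 0.136 | 0.135 | 0.151 | 0.160 (p = 0.50) |
| Phase III, nominal 0.05 | 0.033 | 0.035 | 0.036 | 0.037 (p = 0.62) |

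**Step 4: Boschloo's test.** Order the tables by the Fisher P value and take the largest cut-off c for which the maximum size over p stays within α.

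- n = 57: c = 0.2535, maximum size 0.199.
- n = 91: c = 0.0672, maximum size 0.049.

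Both cut-offs exceed the nominal α, so every table that Fisher rejects is also rejected here.

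**Step 5: power at the same N** (rejections in the correct direction).

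| | Fisher | Boschloo | Gain |
|---|---|---|---|
| Phase II, 57 per arm | 80.7% | 84.9% | 4.2 points |
| Phase III, 91 per arm | 80.8% | 84.1% | 3.4 points (0.8414 − 0.8076) |

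**Step 6: a table where the decision differs.** With 13/57 versus 20/57 progressing, Fisher gives P = 0.215, so the gate is not passed at 0.2. Since 0.215 is below 0.2535, Boschloo rejects.

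**Step 7: alternatives.** Barnard's test ordered by the pooled z statistic has Phase II power of 82.4%, a gain of only 1.7 points, and Phase III power of 84.1%. The uncorrected Pearson chi-square reaches a maximum size of 0.242 and 0.052, so it does not hold either level.

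**The case against.** The strongest reply is that the protocol states nothing false. Alpha is a ceiling, not a target. Any exact test on discrete data falls below it, Boschloo's included. The sample sizes suit the named test, since 57 per arm is where Fisher's power first passes 80%. Fisher's test for a two-by-two primary comparison is standard and valid. All of this stands, and it is why the point is a suggestion and not a correction.

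Three stronger readings are tempting, and the protocol supports none of them.

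- A reader might infer that the stated error rates are wrong. They are not: 0.160 and 0.037 both respect the limits of 0.2 and 0.05.
- A reader might infer that an effective treatment is dropped more often than planned. The plan accepts a 20% miss rate, and Fisher misses 100 − 80.7 = 19.3% and 100 − 80.8 = 19.2% under the design rates. The loss exists only relative to a different test.
- A reader might multiply the powers and say that the chance of passing both phases rises from 65% (0.807 × 0.808) to 71% (0.849 × 0.841). That assumes separate patients in the two phases. The protocol does not say whether the 114 count towards the 182, so the product is not part of this point.

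It is also fair to object that the extra power is not free. Boschloo raises the Phase II maximum two-sided false-positive rate from 0.160 to 0.199, so an ineffective treatment could enter Phase III somewhat more often. That is within the level the protocol chose, but it is the direct price of the gain and should be weighed openly. Finally, randomization is stratified by age and sex. If the primary analysis were stratified instead, this choice between unstratified tests would no longer arise.

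**Conclusion.** The point holds as a cheap, optional improvement. The Fisher test is valid and adequately powered as planned, but it uses at most 0.160 of 0.2 and 0.037 of 0.05. Boschloo's test, with the same guarantee and the same N, adds 4.2 points of power in Phase II and 3.4 in Phase III.

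The size rests on three assumptions: the design rates of 20% and 40%, the full evaluable numbers with equal arms, and an unstratified comparison. The gain belongs to Boschloo's test in particular and does not carry over in full to every unconditional exact test.

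**What to change.** In the primary endpoint paragraph, replace the Fisher exact test with Boschloo's unconditional exact test for the unstratified comparison, at two-sided 0.2 at the end of Phase II and two-sided 0.05 at the end of Phase III. Specify the test and its level, not a fixed cut-off, because the cut-off depends on the arm sizes actually reached.

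The change takes one sentence, standard software and no extra patients. It should be made before outcome data are seen, because outcome assessors and data analysts are unmasked and a later change of test would be hard to defend. The costs are a P value that readers know less well and the higher Phase II false-positive ceiling. If the sponsor prefers to keep Fisher's test for familiarity or for its stricter gate, the plan remains sound. Uncorrected chi-square should not be used as the substitute.

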**Secondary endpoints**

Descriptive results will be presented as means  $\pm$  standard deviation (SD), medians with interquartile range (IQR), and percentages with 95% confidence intervals (CI). Chi-square or Fisher's exact test will be used to compare categorical variables. ANOVA and Student's t-test will be used for continuous variables unless they will be not normally distributed, in which case the Kruskal-Wallis or Mann-Whitney test will be used to compare continuous parameters. Kaplan-Meier product-limit estimates will be used to calculate time to different secondary endpoints. The log-rank test will be used to assess the difference between the survival curves among arms. Changes in some biomarkers respect to baseline values will be compared using paired Wilcoxon test. The association between primary outcome and transfusion dose of CCP expressed as ml/kg of the recipient body weight, adjusted for anti-Sars-CoV-2 neutralizing and ELISA antibody concentrations, will be investigated through regression analysis. All tests will be two-sided and a P value inferior to 0.05 will be regarded as significant.

**Analysis settings** Analysis will be carried out in the "intention to treat" set.

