that COVID-19 rapidly deteriorate in specific categories of patients. Poor prognosis patients are aged over 60, are mainly man and near half of them have some comorbidities. In-hospital death is associated with older age, higher Sequential Organ Failure Assessment (SOFA) score and blood d-dimer greater than 1 µg/mL. These findings are known to be associated with severe pneumonia. Although current best estimate is that about 81% of people with COVID-19 have mild disease and never require hospitalization, 14% of patients have severe illness and need oxygen therapy, and approximately 5% require intensive care treatment and mechanical ventilation. Since the reported case fatality rate ranges from 49% to 97% in critical patients, it is pivotal to find alternative strategies to prevent older patients and patients with chronic morbidities from worsening. The association between severe COVID-19 and specified patient characteristics has emerged from the analysis of large patient population and from meta-analysis of recently published studies. Older age is an independent poor outcome predictor in hospitalized patients (odds ratio 1.10, 95% CI 1.03–1.17 per year increase). Among 72,314 COVID-19 cases, case fatality rate was 2.3% in total population, 8% in people aged 70 to 79, and 14.8% in those aged 80 and older. In the whole population, case-fatality rate was higher in people with comorbidities, ranging from 5-6% in persons with hypertension, chronic respiratory disease, diabetes or cancer, up to 10% in those with cardiovascular diseases. On the other side, one or more comorbidities was reported in 36/54 (67%) poor outcome COVID-19 patients as compared to 55/137 (40%) survivors ( $p=0.0010$ ). These overall data show that elderly people with comorbidities are most susceptible to severe COVID-19 and therefore, should be protected by approaches which may supplement current therapies. Data relative to the long lasting persistence of the virus in patients with poor outcome, together with the presence of lymphopenia (CD4+T and CD8+ T cells) and exaggerated pro-inflammatory and anti-inflammatory cytokines (IL-2R, IL-6, TNF- $\alpha$  and IL-10) suggest that disease severity and outcome of COVID-19 is due to the SARS-CoV-2-induced cytokine storm. Sars-CoV-2 seems able to induce a functional exhaustion of specified T and NK lymphocyte subpopulations, breaking down antiviral immunity. One possible explanation is that the immune system of elderly people,

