### Secondary outcomes

- Decreased viral load on nasopharyngeal swab (days 6, 9 and 14)
- Decreased viremia at day 6 and 9
- Increased antibody titre against SARS-CoV2 (days 30 and 60)
- Proportion of patients with negative of SARS-CoV2 nasopharyngeal swab (day 60)
- Length of hospital stay
- Mortality rate at day 28
- Total plasma related adverse event (Febrile reactions, TRALI, TACO, TTI) (day 60)
- Total non-plasma related adverse events (day 60)
- Severe adverse events (SAE) (day 60)

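### Length of hospital stay has no rule for in-hospital death, so under the stated tests an early death scores as a short, favourable stay

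*Protocol*

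**What the plan says.** The Protocol's list of phase III secondary outcomes (Outcomes and endpoints) includes "Length of hospital stay" and, as a separate item, "Mortality rate at day 28". The synopsis list of phase III endpoints contains neither.

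The Secondary endpoints paragraph under Statistical methods gives one set of methods for all secondary outcomes:

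- Continuous outcomes: "ANOVA and Student's t-test will be used for continuous variables unless they will be not normally distributed", in which case Kruskal-Wallis or Mann-Whitney applies.
- Times to event: "Kaplan-Meier product-limit estimates will be used to calculate time to different secondary endpoints", followed by "The log-rank test will be used to assess the difference between the survival curves among arms". The endpoints meant are not named.
- Analysis set: intention to treat.

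The Protocol has no rule for in-hospital death in the stay comparison, no censoring rule and no competing-risk method. On background mortality, the Rationale reports that "case fatality rate was 2.3% in total population, 8% in people aged 70 to 79, and 14.8% in those aged 80 and older". Appendix C places death in the worst category of the ordinal scale behind the primary outcome.

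**The concern.** A stay that ends in death is normally shorter than one that ends in discharge home. If length of stay is tested as a plain continuous variable in all randomised patients, death on day 6 looks better than discharge on day 14. An arm with fewer deaths then has fewer of these short stays, and its average rises. This reverses the ordering in the trial's own primary scale, where death is the worst state.

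A related difficulty arises if discharge or swab clearance is analysed as a time to event with deaths censored in the usual way. Censoring treats the dead as patients who could still have gone home or cleared the virus, so the estimated discharge curve does not register the deaths.

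The population is aged 65 or over with comorbidities and pneumonia on CT, so deaths will occur. A flat or longer stay beside an inconclusive mortality result could be read as evidence against the treatment. The assignment is also unmasked to data analysts, so a rule for deaths carries most weight if it is fixed before results are seen.

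**Working it through.** **What the plan gives.** There is no figure for length of stay to reproduce. The trial size comes from the primary endpoint: 91 per arm for 40% v 20%, two-sided alpha 0.05, power 80%. The uncorrected formula gives (1.96·√(2·0.3·0.7) + 0.842·√(0.24 + 0.16))² / 0.2² = 81.2. The continuity correction gives (81.2/4)·(1 + √(1 + 4/(81.2·0.2)))² = 90.9, so 91. That size is used below.

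**Assumptions.** The Protocol gives no stay or time-to-death data. All of these are assumed:

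- lognormal times with log-SD 0.5;
- survivors' median stay of 14 days in both arms, so no effect on stay itself;
- deaths at a median of 6, 8 or 10 days;
- CCP halves mortality;
- control mortality of 8% or 14.8% (the age-specific case fatality in the Rationale) or 20%.

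**Mean stay when a death counts as a stay ending at death.** A lognormal mean is median × exp(0.5²/2) = median × 1.133. With control mortality m and CCP mortality m/2, the difference (CCP minus control) is

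(m/2) × 1.133 × (14 − median day of death).

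Worked case, m = 20%, deaths at median 8 days:

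- survivors' mean 14 × 1.133 = 15.86; mean for deaths 8 × 1.133 = 9.07
- control: 0.8 × 15.86 + 0.2 × 9.07 = 14.5 days
- CCP: 0.9 × 15.86 + 0.1 × 9.07 = 15.2 days

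| Control mortality | Deaths at 6 d | 8 d | 10 d |
|---|---|---|---|
| 8% | +0.36 | +0.27 | +0.18 |
| 14.8% | +0.67 | +0.50 | +0.34 |
| 20% | +0.91 | +0.68 | +0.45 |

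Every entry is a longer mean stay on CCP, in days, although CCP saves lives and does not lengthen any survivor's stay. If deaths occur at a median of 14 days, the same as survivors' stay, the difference is zero.

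**How often this is significant.** Simulated trials of 91 per arm, Mann-Whitney, two-sided 0.05, show a significantly longer stay on CCP in about 3 to 10% of trials at 8 to 14.8% control mortality. At 20% the range is about 5 to 15% (about 14% with deaths at median 6 days, about 9% at 8 days). The chance level in that direction is 2.5%.

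**Loss of power when stay truly shortens.** Suppose CCP also cuts survivors' median stay from 14 to 12.5 days, with deaths at median 7 days. At 20% v 10% mortality, power is about 7% on raw stay and about 60% with deaths ranked worst. At 8% control mortality the contrast is about 21% v 45%. Part of this gain arises because the second analysis counts deaths and so tests a different quantity.

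**Conditional check on the Kaplan-Meier sentence.** Suppose discharge were analysed as a time to event with deaths censored.

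- Lognormal case, 20% v 10% mortality, deaths at median 8 days: a survivor is discharged by day 28 with probability Φ(ln 2/0.5) = 0.917. The true share discharged alive is 0.8 × 0.917 = 73% on control and 0.9 × 0.917 = 83% on CCP. One minus Kaplan-Meier gives about 91% in both arms.
- Constant hazards, discharge at 0.06 per day in both arms: Kaplan-Meier gives 1 − exp(−0.06 × 28) = 81% in both arms whatever the mortality. With 28-day death cut from 20% to 10%, the share discharged alive is 69% v 75%. A significant result favouring CCP occurs in about 2.7% of trials with deaths censored and 12% with deaths kept in the risk set to day 28.

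**The case against.** The strongest reply is that the Protocol is silent rather than wrong. It nowhere says that deaths count as short stays, and handling of deaths is commonly left to the statistical analysis plan, which is not shown. A reader might infer that the Protocol decided to ignore death, and the text does not support that. What stands is narrower: the Protocol does fix the tests and the analysis set, and those tests applied to raw stay in all randomised patients produce the behaviour shown. Restricting to survivors would depart from intention to treat.

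A reader might also infer that the Kaplan-Meier sentence is itself an error. That does not follow. No listed secondary outcome is defined as a time to event, swab negativity is a proportion at a fixed day, and nothing ties length of stay to Kaplan-Meier. For time to death nothing competes, so Kaplan-Meier and log-rank are right. Kaplan-Meier need not censor deaths either: with complete follow-up, keeping them in the risk set to the end gives the cumulative incidence of discharge. A log-rank test with deaths censored is also a valid test of the cause-specific discharge hazard. This part of the point is therefore conditional.

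The effect is small at the fatality the Protocol cites. Those rates are for all cases: inpatients may fare worse, while entry requires a PaO2/FiO2 of at least 300, which points the other way. Raw stay is also a legitimate description of resource use.

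Finally, day-28 mortality is reported separately, so a survival benefit is not lost from the trial. That is true, but mortality may be inconclusive at this size: for 20% v 10%, 0.10/√((0.16 + 0.09)/91) = 1.91, just under 1.96, so power is only about one half. Separate reporting does not correct the stay comparison.

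**Conclusion.** The point holds for length of hospital stay. Under the tests and analysis set in the Protocol, with no rule for deaths, a treatment that prevents deaths can show no benefit or a slightly longer stay. The size is modest: about 0.2 to 0.7 day at 8 to 14.8% control mortality and 0.5 to 0.9 day at 20%, with a significantly longer stay on CCP in about 3 to 10% and 5 to 15% of trials. These figures rest on assumed lognormal stays, equal survivor stays, halved mortality and deaths at a median of 6 to 10 days. The bias shrinks as deaths come later and vanishes when they take as long as discharge.

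For Kaplan-Meier the point holds only if discharge or swab clearance is analysed that way with deaths censored, which the Protocol does not say. It would also go too far to conclude that the trial would miss a mortality benefit or that its main result is at risk. This is one phase III secondary outcome. The primary test, the sample size and the phase II/III decision are untouched, and death already counts in the primary scale. It is a cheap improvement worth making before results are seen.

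**What to change.** In the Secondary endpoints paragraph under Statistical methods:

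1. State how in-hospital deaths enter length of stay. Either rank them worst or replace the outcome by days alive and out of hospital to day 28. Compare arms with the Mann-Whitney test already planned, and report raw stay descriptively.
2. Name the endpoints covered by the Kaplan-Meier sentence. Keep Kaplan-Meier and log-rank for time to death. If discharge or swab clearance is included, estimate it by cumulative incidence (Aalen-Johansen) with death as a competing event, or keep deaths in the risk set to the end of follow-up, and compare arms with Gray's test.

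The cost is wording. Ranking deaths worst needs only dates of discharge and death. Days alive and out of hospital also needs any readmission before day 28, which should be confirmed as recorded. The downside is that the composite is less familiar and answers a slightly different question from raw stay, which is why raw stay should still be shown.

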| Objective                | 
To demonstrate the superiority of COVID-19 convalescent plasma (CCP) plus standard therapy (ST) over ST alone
 

– To prevent progression of pneumonia in COVID-19 patients aged <math>\geq 65</math> with chronic comorbidities

– To decrease viral load

– To raise anti-SARS-CoV-2 antibody titer (ELISA, NAT) in recipients

                                                                                                                                                                                                                                                                                                                                                                                                                                                                                                                                                                                                                                                                                                                                                                                                                                                                                                                                                                 |

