
exposed to chronic stimulation associated with comorbidities, might be more susceptible to this Sars-CoV-2 effect. As a result, in these patients, the activation of the innate immune system might fail to produce an adequate adaptive response (i.e., virus-specific CD8+ T-cells). This could result in a persistent self-induced inflammation that then causes mortality. We therefore hypothesize that transfusing the convalescent plasma containing neutralizing antibodies at an early phase of disease could prevent or switch-off the persistent inflammatory response elicited by the virus, before that cytokine storm exerts devastating effects. As a proof of concept that CCP has an activity on the infection, in enrolled patients we will assess the viral load in blood and nasopharyngeal swab before and plasma infusion.

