#### Screening phase: day -1

#### Baseline visit: day 0:

Physical examination and vital signs (blood pressure, heart rate, respiratory rate, temperature), Respiratory status (pO2/FiO2 and SpO2 at rest if applicable), ECG; blood sampling for ABO groups (on two separate samples), RT-PCR for SARS-CoV-2 on nasopharyngeal swab. routine blood tests (blood count, creatinine, BUN, sodium, potassium, ALT, AST, LDH, fibrinogen, D-dimer, ferritin, CRP), viremia, anti SARS-Cov-2 antibody screening, IL6.

**Plasma administration: days 1,2, 3.** All patients will sign the informed consent to receive blood products in use at each center.

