**Daily study assessment: days 1 to 14**

Physical examination and vital signs (blood pressure, heart rate, respiratory rate, temperature, oxygen supplementation), Respiratory status (pO2/FiO2 and SpO2 at rest if applicable), ECG and chest scan (on day 7 and 14, or additional days if clinically advised); routine blood tests (blood count, creatinine, BUN, sodium, potassium, ALT, AST, LDH, fibrinogen, D-dimers, ferritin, CRP, every three days unless clinically advised), RT-PCR SARS-Cov2 on rhino-pharyngeal swab at the same time points of routine blood tests until 2 consecutive negative swabs within 24 hours, viremia (day 6, day 9, day 12 and day 14), anti SARS-Cov-2 antibody screening (day 14), IL6 (day 3, day 6, day 9).

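### The only test named for biomarker change from baseline compares patients with themselves and makes no comparison of arm A with arm B

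*Protocol*

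**What the plan says.** The trial is randomised 1:1, and the Study Synopsis gives its objective as "To demonstrate the superiority of COVID-19 convalescent plasma (CCP) plus standard therapy (ST) over ST alone", covering progression of pneumonia, viral load and antibody titre. The Rationale proposes that early plasma "could prevent or switch-off the persistent inflammatory response elicited by the virus". It also presents assessment of viral load around the plasma infusion as proof of concept that plasma acts on the infection.

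Blood for inflammatory markers is taken at baseline ("viremia, anti SARS-Cov-2 antibody screening, IL6", with CRP, ferritin and D-dimer among the routine tests). The daily assessment section schedules "IL6 (day 3, day 6, day 9" for follow-up, and routine bloods every three days.

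The Secondary endpoints paragraph of the statistical methods contains three relevant statements:

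- For change from baseline: "Changes in some biomarkers respect to baseline values will be compared using paired Wilcoxon test".
- For continuous variables in general, ANOVA and the t-test, unless the data are not normal, "in which case the Kruskal-Wallis or Mann-Whitney test will be used to compare continuous parameters".
- For all of these: "All tests will be two-sided and a P value inferior to 0.05 will be regarded as significant".

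The arms are named in that paragraph only for time-to-event data: "The log-rank test will be used to assess the difference between the survival curves among arms".

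**The concern.** A paired Wilcoxon test uses each patient as his own control. In acute infection, markers may move over days under standard therapy alone, and the test cannot separate that movement from an effect of plasma. Randomisation supplies a concurrent control group for exactly this purpose, and the paired test does not use it.

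Two misleading results are possible when plasma does nothing: a significant change in arm A, or a significant change in arm A beside a non-significant one in arm B. Under the blanket 0.05 rule either would be reported as significant.

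The affected markers are not named. The sentence says only that it concerns some biomarkers, so it could reach viral load and viremia. Both are listed secondary outcomes, worded as decreases without a comparator. It could equally reach IL-6 and CRP, which are collected but are not listed as outcomes.

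**Working it through.** **Arm sizes.** The protocol gives no figure for any biomarker analysis, so the only stated figures to reproduce are the arm sizes in the Sample size section: 57 per arm (two-tailed alpha 0.2) and 91 per arm (two-tailed alpha 0.05), for 20% versus 40% with 80% power. The pooled-variance formula is

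n0 = [z(1−α/2)·√(2·0.3·0.7) + z(0.8)·√(0.2·0.8 + 0.4·0.6)]² / 0.2²

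It gives 47 and 82 after rounding up. With the continuity correction n = (n0/4)·[1 + √(1 + 4/(0.2·n0))]², the results are 56 and 91. The stated 57 and 91 are therefore reproduced to within one patient, and these sizes are used below.

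**Assumptions.** Change from baseline is normal with SD 1 and has the same mean in both arms, so there is no plasma effect. The natural change is set at 0, 0.2, 0.3, 0.5 and 0.8 SD because the documents give neither an SD nor a trajectory. The tests are two-sided, so a natural rise gives the same results as a natural fall.

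**Simulation.** There were 4,000 trials per setting. Each used a paired Wilcoxon test within each arm at 0.05 and a Mann-Whitney test on the changes, A versus B, at 0.05.

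| Per arm | Natural change (SD) | Paired test significant in A | Significant in A, not in B | A versus B significant |
|---|---|---|---|---|
| 57 | 0 | 4.9% | 4.6% | 5.2% |
| 57 | 0.2 | 30% | 21% | 5.4% |
| 57 | 0.3 | 60% | 25% | 5.0% |
| 57 | 0.5 | 95% | 4.9% | 4.8% |
| 57 | 0.8 | about 100% | 0% | 5.0% |
| 91 | 0 | 5.2% | 5.0% | 5.7% |
| 91 | 0.2 | 45% | 25% | 5.1% |
| 91 | 0.3 | 79% | 17% | 5.6% |
| 91 | 0.5 | 99.5% | 0.4% | 5.4% |
| 91 | 0.8 | 100% | 0% | 4.8% |

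**Hand check of one cell.** For normal changes the signed-rank test behaves approximately like a z test with mean δ·√(3n/π). With n = 57 and δ = 0.3 this is 0.3·√54.4 = 2.21, so the chance of significance is about Φ(2.21 − 1.96) = Φ(0.25) = 0.60, as in the table.

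**Ceiling of the A-only pattern.** With no plasma effect the arms are independent, each with the same chance p of a significant paired test. Significant in A but not in B then has probability p(1−p), which is at most 0.25, at p = 0.5. For example, 0.30·0.70 = 0.21 at 57 per arm and 0.2 SD.

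**The case against.** The strongest reply is that the same paragraph already provides independent-group tests for continuous variables. IL-6, CRP, ferritin and D-dimer levels are continuous, and comparing their follow-up levels between randomised arms would be valid, if less efficient than a baseline-adjusted analysis. This stands in part. A reader might infer that biomarkers are examined only before versus after, or that the anti-inflammatory hypothesis receives no randomised test. The protocol does not support either inference. The general tests are not excluded for these markers, and the hypothesis's clinical consequence, progression, is compared A versus B by Fisher's exact test. What the general sentence does not do is mention change or name the arms, whereas a later and more specific sentence gives change to the paired test.

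A second reply is that no text says a significant paired result will be read as a plasma effect. That is correct. The misreading is a risk and not a stated rule, although the proof-of-concept remark in the Rationale leans towards it. It follows that the 30% to 99.5% figures are the power of the paired test to detect a change that truly occurred. They are not false-positive rates for its own null hypothesis, and become errors only if the result is attributed to plasma.

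A third reply is that transformations, marker lists and time points commonly belong in a statistical analysis plan, which is not at hand. That also stands, and the lack of such detail is not the point here. The point is the test that the protocol does name.

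**Conclusion.** The point holds in limited form. The only test that the protocol names for biomarker change from baseline is within-patient and cannot support superiority over standard therapy. With a natural change of 0.2 to 0.5 SD and no plasma effect, it is significant in arm A in about 30% to 95% of trials at 57 per arm and 45% to 99.5% at 91 per arm. Significance in A but not in B reaches about 25% at most. A between-arm test on change stays at 4.8% to 5.7%.

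These figures depend on the assumed size of natural change and on normal change scores; with no natural change the paired test is significant in about 5%. That a paired test contains no arm comparison depends on neither assumption.

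The matter concerns secondary and exploratory analyses. The primary analysis, the sample size and the decision to proceed to phase III are unaffected. The change is worth making but is not critical to the trial.

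**What to change.** Replace the paired-test sentence with a between-arm comparison. Biomarker values after baseline would be compared A versus B, adjusted for the day 0 value, by ANCOVA on the log scale or by rank ANCOVA. This would cover IL-6 at days 3, 6 and 9, and CRP, ferritin, D-dimer, viral load and viremia at their scheduled days. Within-arm paired changes can remain as description, without a significance claim.

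The cost is one sentence in the Secondary endpoints paragraph. The baseline and follow-up samples are already scheduled, and no patients need be added. Naming one marker at one day as the lead test of the inflammatory hypothesis is optional. It would go beyond that one sentence, since it would in effect add an outcome to the lists in the synopsis and in the outcomes section.
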